### Randomization

To prevent larger centers from disproportionately influencing the findings, we will implement randomization in centers expected to enroll more than one hundred patients during a given period, based on the focus of each phase.

### Statistical analysis

Descriptive statistics will be used to describe patient demographics and baseline characteristics, types of respiratory support used, device settings, and respiratory variables and parameters, including measures of oxygenation and decarboxylation. Continuous variables will be expressed in medians and interquartile ranges, and categorical variables will be expressed in frequencies and proportions. The Kruskal-Wallis test will be used to compare continuous variables, and the Chi-squared test will be used for categorical variables.

Respiratory support settings and respiratory variables and parameters at successive days will be reported in detail for the first days of respiratory care and compared between different age groups, i.e., neonates (< 1 month), infants (1 month to < 12 months), toddlers (12 months to < 3 years), preschoolers (3 years to < 6 years), school-age children (6 years to < 12 years), and adolescents (12 years to 18 years). Additionally, respiratory support settings, respiratory variables, and ventilation parameters will be compared between patients with and without PARDS and across other patient groups, including patients receiving respiratory support due to a pulmonary disease *versus* non-pulmonary conditions and patients receiving ECMO.

Key respiratory support settings, respiratory variables, and parameters will be visualized using cumulative distribution plots for the first days and line graphs over successive days. Inpatient trends over time are assessed with mixed-effect linear models with patients treated as a random effect to account for clustering and repeated measurements, and with day, different patient group and their interaction as fixed effects. P values from this analysis represent the overall difference among different patient groups over time, and p values from interaction represent the difference in trend over time among the different patient groups.

Time-to-event outcomes, like liberation from the ventilator, discharge and death, will be presented in Kaplan-Meier curves. Cox proportional hazard modelling or competing risk analyses will be used to study associations with continuous clinical outcomes, presented as hazard ratios (HR) and 95% confidence intervals (95%CIs). Logistic regression will be used to study the association between key ventilator settings and ventilation parameters and binary clinical outcomes, and will be presented as odds ratios (OR) and 95%CIs.

A robust locally weighted scatter plot smoothing (LOWESS) method will be used to investigate the association between ICU mortality and key ventilatory variables and parameters, including V^T^, Ppeak, PEEP, FiO^2^, RR, PaO^2^/FiO^2^, ΔP, MP and ME. The smoothing curves will be generated with a bandwidth of 0.66, a polynomial regression with 1 degree of freedom, and a tricubic weighting function so that observations furthest from the point of interest are assigned the least weight.

In a univariate analysis, the impact of the single key ventilatory variables on mortality will be assessed by estimating the relative risk of all-cause 28-day ICU mortality. Multivariate logistic regression will be used for the adjusted analysis, adjusting for unequal distribution of effect modifiers. We will adjust for baseline covariates selected according to clinical relevance, including age, sex, weight, comorbidities, and severity of illness. Results will be shown as ORs with 95%CI. Multiple imputation will be performed to account for missing values.

Data will be analyzed with R version 4.2.2 (R Core Team, 2022, Vienna, Austria). Statistical uncertainty will be expressed by 95%CIs. A p value < 0.05 is considered statistically significant.

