### Study endpoints

The study endpoints vary based on the study's evolving scope. Since the scope of the initial phase of PRoVENT-PED is invasive ventilation, key endpoints include a set of ventilator settings and ventilation parameters, such as tidal volume (V_T_); maximum (Pmax), peak (Ppeak), plateau (Pplat) and mean airway pressures (Pmean); positive end-expiratory pressure (PEEP); fraction of inspired oxygen (FiO^2^); and respiratory rate (RR) at fixed time points over the first four days of invasive ventilation. Driving pressure (ΔP), respiratory system compliance (C_RS_), and measures of ventilation intensity are calculated daily from these data. Other endpoints include duration of ventilation in survivors and nonsurvivors, the number of days free from invasive ventilation and alive at day 28, length of stay in ICU and hospital, and mortality rates in ICU and hospital and at day 28.

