The most used ventilation mode was PCV (92%) (Table 2). Most patients received V_T_ of less than 8mL/kg, with younger children receiving lower median V_T_ than older patients (Figure 2). Younger patients received lower median PEEP than older patients. Median FiO_2_ and median RR were higher, and median ΔP was lower in younger children. PARDS patients received lower V_T_, higher median PEEP and FiO_2_, and lower median ΔP than non-PARDS patients.

**Table 2 t2:** Ventilator settings, ventilation variables and parameters, and arterial blood gas analysis at day 0

		All n = 125	Neonates n = 10	Infants n = 61	Toddlers n = 14	Preschoolers n = 8	School-aged n = 16	Adolescents n = 16
Ventilation mode								
	Volume controlled ventilation	9 (7)	0 (0)	0 (0)	0 (0)	1 (13)	5 (31)	3 (19)
	Pressure controlled ventilation	115 (92)	10 (100)	60 (98)	14 (100)	7 (88)	11 (68)	13 (81)
	Volume support	1 (1)	0 (0)	1 (2)	0 (0)	0 (0)	0 (0)	0 (0)
Ventilator settings								
	V_T_ (mL/kg ABW)	6 [5 - 7]	6 [5 - 6]	6 [5 - 7]	7 [4 - 8]	9 [7 - 9]	7 [6 - 8]	6 [5 - 7]
	PEEP (cmH_2_O)	6 [5 - 8]	7 [5 - 8]	6 [5 - 8]	7 [6 - 8]	7 [6 - 8]	6 [5 - 8]	7 [5 - 9]
	RR (breath/min)	30 [25 - 36]	36 [35 - 38]	35 [30 - 40]	29 [26 - 33]	26 [22 - 30]	20 [20 - 25]	19 [15 - 24]
	FiO_2_ (%)	40 [30 - 50]	45 [36 - 58]	40 [30 - 50]	40 [40 - 45]	38 [29 - 45]	30 [30 - 40]	45 [39 - 63]
Ventilation variables and parameters								
	Ppeak (cmH_2_O)	23 [20 - 27]	23 [20 - 26]	24 [21 - 27]	26 [22 - 30]	24 [18 - 26]	20 [17 - 26]	21 [19 - 28]
	Pmean (cmH_2_O)	12 [10 - 14]	10 [10 - 13]	12 [11 - 14]	13 [11 - 16]	13 [10 - 15]	10 [9 - 13]	11 [8 - 13]
	etCO_2_ (kPa)	6 [5 - 7]	5 [3 - 6]	6 [6 - 7]	6 [5 - 7]	5 [5 - 5]	5 [4 - 6]	5 [5 - 6]
	C_RS_	3 [2 - 7]	1 [1 - 2]	2 [1 - 3]	4 [3 - 5]	6 [5 - 10]	15 [11 - 18]	23 [20 - 26]
	ΔP (cmH_2_O)	16 [14 - 19]	17 [12 - 18]	17 [15 - 19]	18 [15 - 22]	17 [13 - 21]	13 [10 - 18]	14 [10 - 19]
	MP (J/minute)	2 [1 - 5]	1 [1 - 1]	2 [1 - 2]	3 [3 - 5]	5 [3 - 5]	5 [4 - 8]	8 [6 - 10]
	ME (mJ/kg)	9 [7 - 11]	10 [6 - 10]	8 [7 - 10]	11 [7 - 14]	11 [10 - 14]	10 [8 - 12]	9 [7 - 10]
Arterial/capillary blood gas analysis								
	pHa	7.4 [7.3 - 7.4]	7.4 [7.3 - 7.4]	7.3 [7.3 - 7.4]	7.3 [7.3 - 7.4]	7.4 [7.3 - 7.4]	7.4 [7.3 - 7.4]	7.4 [7.4 - 7.4]
	PaO_2_ (kPa)	6.7 [6.3 - 6.7]	5.2 [5.2 - 5.3]	6.7 [6.0 - 6.7]	6.7 [6.7 - 6.7]	6.7 [6.7 - 6.7]	6.7 [6.7 - 6.8]	6.7 [6.7 - 6.7]
	PaCO_2_ (kPa)	5.8 [5.2 - 6.6]	5.8 [5.4 - 6.3]	6.6 [5.6 - 6.7]	6.1 [5.8 - 6.3]	4.5 [4.2 - 5.2]	5.1 [4.7 - 5.7]	5.2 [5.0 - 5.7]

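### Trend model with no allowance for unequal variance by age group: interaction p values for C_RS, MP and ΔP are likely to be too small if it is fitted on the raw scale

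*Protocol article*

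**What the plan says.** Under Statistical analysis, the article specifies the model for the daily course of ventilator parameters as follows: "Inpatient trends over time are assessed with mixed-effect linear models with patients treated as a random effect to account for clustering and repeated measurements". The fixed effects are day, patient group and their interaction. Two p values are given a meaning. One is the overall group difference over time. For the other, "p values from interaction represent the difference in trend over time among the different patient groups". The threshold is also fixed: "A p value < 0.05 is considered statistically significant". The measurements are taken "at fixed time points over the first four days of invasive ventilation".

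The section names no residual variance structure, no transformation and no robust standard error. For description it says "Continuous variables will be expressed in medians and interquartile ranges".

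Under Calculations, C_RS and MP are computed from tidal volume in absolute units (equations 4 to 7), whereas mechanical energy (ME) is per kilogram. Pilot Table 2 gives the age groups as "Neonates n = 10 Infants n = 61 Toddlers n = 14 Preschoolers n = 8 School-aged n = 16 Adolescents n = 16" and the day-0 quartiles of C_RS as "1 [1 - 2] 2 [1 - 3] 4 [3 - 5] 6 [5 - 10] 15 [11 - 18] 23 [20 - 26".

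**The concern.** A linear mixed model with a patient random intercept, fitted in the usual way, estimates one residual variance for all groups. The standard error of each group's trend is built from that pooled value. When groups differ in both size and variance, the pooled value is dominated by the largest group. Here that is the infants: 61 of 125, or 49% of the pilot. If the largest group has low variance, the standard errors of the smaller, more variable groups are too small. The interaction test then rejects too often even when every group has the same trend.

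For C_RS and MP there is a structural reason to expect this. Both scale with body size, so it is implausible that day-to-day variation has the same absolute size in a neonate and an adolescent. For ΔP the reason is empirical only: its pilot IQR is narrowest in infants and wider in every other group.

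At stake are the age-group comparisons of trend in parameters that the article lists among its endpoints. A larger sample does not help, because the error rate depends on group shares and variance ratios, not on N.

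**Working it through.** **Inputs from the article**
- Group sizes 10, 61, 14, 8, 16, 16 (Table 2), used as shares p_g = 0.080, 0.488, 0.112, 0.064, 0.128, 0.128.
- Four daily measurements; nominal level 0.05.
- Day-0 IQR widths from neonates to adolescents (Table 2): C_RS 1, 2, 2, 5, 7, 6; ΔP 6, 4, 7, 8, 8, 9; MP 0, 1, 2, 2, 4, 4. The neonatal MP width is zero after rounding and is replaced by 0.5; using 0.2 or 1 leaves the result at 0.17.

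**Assumption.** The within-child residual SD s_g is proportional to the IQR width. The article reports no within-patient variance.

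**Method.** With linear day, the interaction is a 5-df Wald test of equal slopes. Its true covariance is V = C diag(s_g²/n_g) C′. The model uses V₀ = C diag(s̄²/n_g) C′, with s̄² = Σ p_g s_g². Under identical trends the statistic is a sum of five independent chi-squares on 1 df, weighted by the eigenvalues of V₀⁻¹V. It is compared with 11.07, the 95% point of chi-square on 5 df. The weights add up to Σ(1 − p_g)s_g²/s̄², which equals 5 when variances are equal.

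**Benchmark.** Equal variances give a rejection rate of 0.050, so the nominal level reproduces.

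**Pooled variances**
- C_RS: 0.080×1 + 0.488×4 + 0.112×4 + 0.064×25 + 0.128×49 + 0.128×36 = 14.96. The infants' own value is 4; that of school-aged children is 49.
- ΔP: 0.080×36 + 0.488×16 + 0.112×49 + 0.064×64 + 0.128×64 + 0.128×81 = 38.83. Infants 16; adolescents 81.
- MP: 0.080×0.25 + 0.488×1 + 0.112×4 + 0.064×4 + 0.128×16 + 0.128×16 = 5.31. Infants 1; school-aged and adolescents 16.

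**Rejection rate of the 5% interaction test when all trends are identical**

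| Parameter | Sum of weights (5 if equal) | SD follows IQR | SD differences halved on log scale | Group-specific variances (simulated) |
|---|---|---|---|---|
| C_RS | 6.95 | 0.181 | 0.118 | 0.046 |
| MP | 6.77 | 0.171 | 0.120 | 0.052 |
| ΔP | 6.98 | 0.163 | 0.108 | 0.048 |

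Simulating 3,000 patients over four days (3,000 runs) with the pooled variance gave 0.177, 0.163 and 0.161 for C_RS, MP and ΔP, in agreement with the formula.

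**Sensitivity**
- If groups differ only in between-patient spread and share one residual variance, the rate is 0.05, because the random intercept cancels from the trend contrast.
- If s_g follows the group median, or its square root, instead of the IQR: C_RS 0.19 or 0.16; MP 0.18 or 0.12.
- If day is categorical (15 df): C_RS 0.284, ΔP 0.272, MP 0.264.
- On the log scale with one pooled variance, and SD taken from the log quartile ratios: C_RS 0.005, MP 0.018. The error then lies in the other direction.
- Pilot noise: with truly equal variances and the pilot group sizes, this plug-in method gives 0.008 to 0.154 in 95% of pilots. The three values above exceed that range. Once quartiles are rounded to whole units, the upper limit is 0.157 to 0.184, depending on the size of the IQR relative to the rounding. The pilot spreads alone are therefore weak evidence. For C_RS and MP the body-size argument carries the point; ΔP rests on its pilot spread.

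**The case against.** The strongest objection is that the article never says that the residual variance is common. Variance structure is often left to the analysis plan. This stands in part: silence alone would be no finding. But the article fixes the model family, the random effect and the meaning of its p values. Fitted as written on the raw scale, that model has one residual variance, which is a poor fit for quantities that the article defines in absolute units.

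The second objection is that Table 2 shows day-0 spread between patients, while the interaction test depends on day-to-day variation within patients. This stands fully. Table 2 cannot demonstrate the error rate, and if only between-patient spread differs, the interaction test is sound. In that case the exposed p value is the one for the overall group difference, which the article also interprets; its size was not computed here.

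A reader might also infer that RR is tested too conservatively, because its quartiles are "36 [35 - 38] 35 [30 - 40] 29 [26 - 33] 26 [22 - 30] 20 [20 - 25] 19 [15 - 24" and the plug-in rate is 0.015. The same reader might infer that V_T (0.099) and ME (0.139) are tested too liberally. All three lie within the 0.008 to 0.154 that chance alone produces, so no error rate is established for them. Nor is one established for PARDS versus non-PARDS: the text gives no spreads by PARDS status, and any variance ratio would be invented.

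Using medians for description and a linear model for trends is not in itself a contradiction. Skewness is a different matter from unequal residual variance and is not part of this point.

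Finally, the sample size rests on mortality modelling, and the article claims associations only. That limits the consequence, but the article still sets a significance threshold and says what these p values mean.

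**Conclusion.** The point holds conditionally, for C_RS, MP and ΔP across the six age groups. A raw-scale model with one residual variance is likely to give interaction p values that are too small. The 5% test rejects about 16–18% of the time if within-child SD follows the day-0 IQR, about 11–12% if the SD differences are halved on the log scale, and 5% if only between-patient spread differs.

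These figures rest on a common residual variance (implied by the model, not written), on within-child SD tracking an observed cross-sectional spread, and on pilot age shares carrying over to the full study. The case is strongest for C_RS and MP and weaker for ΔP. It would go too far to say that the plan has a known error rate of two to three and a half times nominal, or that the problem covers all key parameters.

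**What to change.** In Statistical analysis, state that the group and interaction p values come from mixed models with group-specific residual and random-effect variances, or from models with patient-level cluster-robust standard errors. Either choice covers both p values, whichever variance component differs. In the simulation, allowing group-specific variances brought the interaction test back to 0.046–0.052 for the three parameters.

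A log scale for C_RS and MP is optional. It changes the question from absolute to relative trends, and with one pooled variance it does not replace the fix.

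The cost is one sentence in the analysis section and a variance option in the R models already planned. No new data are needed.

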### Data collection

All data to be collected are part of standard clinical care. Throughout each phase of the study, the data collected will be tailored to align with the evolving focus of the research, ensuring that it remains relevant and reflects the specific objectives of each stage. At admission, we will collect data on patient demographics - including age, gestational age, sex, height and weight, comorbidities, and baseline characteristics - including reasons for intensive care unit (ICU) admission, and the start of respiratory support, presence of the pediatric acute respiratory distress syndrome (PARDS), and disease severity scores. For 4 days, beginning with the day of start of respiratory support, daily data will be collected at a time in the morning - including data on respiratory support and the respiratory status. Follow-up will be until day 28 to collect outcome data, including the date of stop of respiratory support, date of ICU discharge, and life status at ICU discharge or at day 28, whichever comes first.

Investigators will transcribe all collected data into a web-based electronic Case Report Form (eCRF) (Castor Electronic Data Capture, Amsterdam, the Netherlands).^(22)^ The eCRF complies with all applicable laws and regulations. Transcription will only take place in a secure environment. Directly identifying personal data will be separated from the research data and replaced by an assigned code. The directly identifying data will only be used to contact the patients and will only be available to the local investigators. Access to the assigned codes linked with personal data will be password-protected, restricting access to only the data directly related to the local investigator.

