## RESULTS

Of 398 patients screened, 125 were eligible for this pilot study, 91 from the UMCG and 34 from the AUMC (Figure 1S - Supplementary Material). The main reason for exclusion was not receiving invasive ventilatory ventilation. Patients were predominantly male, and most patients were neonates or infants (Table 1). The most common comorbidities were pulmonary diseases, syndromes, and genetic abnormalities. Most patients were admitted to the ICU and intubated due to pulmonary conditions, and 11% met PARDS criteria. All-cause 28-day ICU mortality was 8%, the median duration of ventilation was 4 [2 - 10] days, and the median length of ICU stay was 5 [3 - 11] days.

**Table 1 t1:** Patient demographics, baseline characteristics and outcomes

Variables		
Patient demographics		
	Age (months)	8 [2 - 72]
	Sex (male)	80 (64)
	Body weight (kg)	8 [5 - 22]
	Body height (cm)	74 [55 - 120]
	Premature birth	14 (11)
Disease severity score		
	PIM III	1 [0 - 2]
Medical history		
	Pulmonary	26 (22)
	Cardiac	23 (18)
	Neuromuscular	5 (4)
	Syndrome or genetic abnormalities	32 (26)
	Oncologic	1 (1)
	Organ transplant	8 (7)
	Chronic ventilation	2 (2)
	Mental retardation	6 (5)
Reason for ICU admission		
	Respiratory	70 (57)
	Cardiac	8 (7)
	Neuromuscular	4 (3)
	Postoperative	32 (26)
	Home ventilation	1 (2)
	Renal failure	3 (2)
	Trauma	6 (5)
	Intoxication	1 (1)
Main reason for invasive ventilation		
	Respiratory	65 (52)
	Circulatory	13 (10)
	Neurological	9 (7)
	Metabolic	1 (1)
	Postoperative weaning	33 (26)
	Trauma	4 (3)
Barotrauma during admission		
	Pneumothorax	3 (3)
	Subcutaneous emphysema	1 (1)
	Pneumomediastinum	1 (1)
Tracheostomy		3 (2)
Discharged		106 (85)
Destination of discharge		
	ICU of another hospital	5 (4)
	Ward	91 (72)
	Other healthcare facility	6 (5)
	Home	4 (3)
Duration of ventilation (days)		4 [2 - 10]
Length of ICU stay (days)		5 [3 - 11]
28-day mortality		10 (8)

PIM III - Pediatric Index of Mortality III; ICU - intensive care unit. Data presented as median with interquartile range [25^th^ - 75th quartile] or n (%).

Median time to collect all data per patient was 20 [15 - 25] minutes (Table 1S - Supplementary Material), the amount of missing data was low (Table 2S - Supplementary Material) and considered acceptable, and local investigators expressed no difficulties using Castor EDC as eCRF for data entry.

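### With patient as the only stated random effect, the day-by-group p value for a difference in trend can be anti-conservative if children's slopes vary or adjacent days are more alike, mainly when day is linear

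*Protocol article*

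**What the plan says.** In the protocol article, Statistical analysis, trends within patients over successive days are to be assessed with "mixed-effect linear models with patients treated as a random effect to account for clustering and repeated measurements", "with day, different patient group and their interaction as fixed effects". The article then fixes how the result is read: "p values from interaction represent the difference in trend over time among the different patient groups". The threshold, in the same section, is "A p value < 0.05 is considered statistically significant".

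Data collection gives the repeated measurements: "For 4 days, beginning with the day of start of respiratory support, daily data will be collected at a time in the morning". Each child therefore contributes up to four values.

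The Statistical analysis section lists six age groups for comparison. It adds that settings and parameters "will be compared between patients with and without PARDS and across other patient groups", including pulmonary versus non-pulmonary disease.

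No random slope, residual covariance structure or robust variance is mentioned. Whether day is a number or a four-level factor is not stated.

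**The concern.** Patient as the sole random effect is ordinarily fitted as a random intercept. The intercept absorbs a child's overall level. It leaves no room for children in the same group to change at different rates, and it makes day 0 as strongly correlated with day 3 as with day 1.

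The interaction is meant to test whether mean trends are equal. Under a random intercept, the reference distribution is right only if three things hold together: mean trends are equal, no child departs from the group slope, and there is no serial correlation. Ventilator settings are adjusted child by child, and one morning's value tends to resemble the previous morning's. If either feature is present, part of the true variance of a child's slope is missing from the interaction's standard error. The test can then reject because children differ within groups rather than because groups differ.

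At stake is the stated p value for a difference in trend by age group, PARDS status and the other groupings, and the width of any interval for a slope difference. More patients do not help, because the ratio of true to assumed variance does not depend on the sample size.

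**Working it through.** **Inputs from the article.** Level 0.05; four daily values, days 0 to 3; two groups (PARDS or not) or six age groups. For simulation, the pilot splits: "11% met PARDS criteria", and age groups of 10, 61, 14, 8, 16 and 16 out of 125 (Table 2).

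**Assumptions, not in the article.** Day linear and equally spaced; slope SD τ relative to residual SD σ; or serial AR(1) correlation ρ. All are shown as ranges.

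**Step 1. Slope variance.** Centred days are −1.5, −0.5, 0.5, 1.5, with sum of squares 5. With four complete days:

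- true variance of a child's estimated slope: σ²/5 + τ²
- variance used by a random-intercept model: (σ² + 5τ²/3)/5 = σ²/5 + τ²/3
- ratio R = (σ²/5 + τ²)/(σ²/5 + τ²/3), which rises from 1 towards 3
- actual level with k degrees of freedom: P(χ²ₖ > c/R), where c is the 95% point: 3.841 for k = 1 (two groups), 11.07 for k = 5 (six groups)

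**Step 2. Reproduce the nominal level.** At τ = 0, R = 1 and the level is exactly 5%. Simulated restricted maximum likelihood (REML) fits of the random-intercept model (about 600 children, 800 runs per cell) gave 4.3% to 6.5% over all settings at τ = 0.

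**Step 3. Let slopes vary.** At τ/σ = 0.5, R = 0.45/0.2833 = 1.588. Two groups: P(χ²₁ > 2.419) = 12.0%. Six groups: P(χ²₅ > 6.970) = 22.3%.

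| τ/σ | R | two groups | six groups |
|---|---|---|---|
| 0.1 | 1.033 | 5.4% | 5.7% |
| 0.2 | 1.125 | 6.5% | 8.0% |
| 0.3 | 1.261 | 8.1% | 11.8% |
| 0.5 | 1.588 | 12.0% | 22.3% |
| 0.75 | 1.968 | 16.2% | 34.4% |
| 1 | 2.250 | 19.1% | 42.6% |
| limit | 3 | 25.8% | 59.5% |

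Simulation with complete data agrees. At 0.5 and 1 it gives 12.3% and 18.1% (two groups), and 22.4% and 43.6% (six groups). With an assumed early stop of ventilation it gives 11.3% and 19.0%, and 25.6% and 44.8%.

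**Step 4. Serial correlation instead of varying slopes.** With correlation matrix C, entries ρ^|i−j|, and centred-day vector d, the true slope variance is d′Cd/25. The model uses [(4 − S/4)/3]/5, where S is the sum of all entries of C. At ρ = 0.5, d′Cd = 4.9375, giving 0.1975. S = 8.25, giving 0.1292. So R = 1.529, and the level is 11.3% (two groups) or 20.3% (six groups).

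| ρ | R | two groups | six groups |
|---|---|---|---|
| 0.3 | 1.314 | 8.7% | 13.4% |
| 0.5 | 1.529 | 11.3% | 20.3% |
| 0.7 | 1.740 | 13.7% | 27.3% |
| 0.9 | 1.943 | 16.0% | 33.7% |

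Separate simulations at ρ = 0.5, 0.7 and 0.9 (500 runs per cell) gave 11%, 13% and 15% for PARDS, and 17%, 30% and 33% for age groups.

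**Step 5. Day as a four-level factor.** With complete data and τ/σ from 0.25 to 2, simulated levels are 5.1% to 8.3% (two groups) and 4.3% to 11.5% (six groups). With assumed early stop they reach 11.9% and 20.8% at τ/σ = 2.

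**Step 6. Does a random slope repair it?** Testing per-child slopes, which with complete data is equivalent to adding the random slope, gives 5.4% and 4.8% (two groups) and 4.8% and 5.1% (six groups) at τ/σ = 0.5 and 1. Under AR(1) with ρ = 0.7 (400 children, 11% PARDS, 150 runs), a fitted random-intercept model rejected in 12.0% of runs. Random intercept plus slope rejected in 4.7%.

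**The case against.** The strongest reply is that the article never says intercept only. It does not exclude random slopes or a serial covariance, and a journal article may leave such detail to a fuller plan. That is right as far as it goes, and the point rests on the ordinary reading. But the article goes beyond naming a method: it states the random effect, gives its purpose as handling repeated measurements, lists the fixed effects and says what the interaction p value means. An analyst who follows that text in the usual way gets the test examined here.

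The second reply is that the size rests on unstated quantities. This stands. The Definitions section labels days rather than measuring time. Day 0 is the day support starts and Day 1 the first full calendar day, so the first gap need not equal the later ones, and a categorical day is a natural reading. Under it the inflation is mostly small. The phrase about difference in trend favours a linear term but does not settle the matter.

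A reader might infer that the test rejects at some fixed multiple of 5%, say two to seven times. The document does not support that. With linear day and varying slopes, the multiple runs from 1.0 up to 5.2 for two groups and 11.9 for six, depending on τ/σ. Nor can one say that the initial phase will report false trend differences; that needs variances that are not given.

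The third reply is that this analysis is secondary. That also stands. The initial phase is sized for the logistic model of ICU mortality. The article also plans day-by-day comparisons and line graphs, so the interaction p value is not the only description of time courses.

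**Conclusion.** The point holds conditionally. If the model is fitted with a random intercept only and day is linear, the interaction test is anti-conservative whenever slopes vary within groups or nearby days are more alike than distant ones.

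The size is worth acting on over the assumed middle range: roughly two to four times nominal for two groups and four to nine times for six age groups at τ/σ of 0.5 to 1, with similar or somewhat lower figures under serial correlation. It is negligible to minor at a ratio of 0.2 or less, and absent if the equal-correlation assumption is true. A four-level day largely removes it with complete data, less so with early stop and large slope variation.

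This merits a change to the stated model, but it does not threaten the study's main mortality analysis.

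**What to change.** In Statistical analysis, make two additions to the trend model:

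1. State whether day enters as a linear term or as a four-level factor.
2. If linear, specify a random intercept and a random slope for day per patient, with unstructured covariance between them. If day is categorical, or the random-slope model does not converge, specify an AR(1) or unstructured residual covariance across the four days. Take the interaction p value from that model.

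The cost is a sentence of wording and a small change to the model code, with no new data. The convergence fallback will sometimes be needed, and fewer interactions will reach significance.
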